### 19.2 Sensitivity Analysis

The following sensitivity analyses for the primary efficacy outcome will be conducted:

[figure not shown]

1. Comparison of the clinical response rates at Day 4 between treatment groups in the MITT analyses set using the Miettinen-Nurminen statistic stratified by the randomisation factor: PORT Risk Class: I (ineligible for study), II (eligible), III (eligible), IV (score of 91-105 eligible and 106-130 ineligible) and V (ineligible for study). Stratum classes for PORT score are II and III/IV.
2. Subjects with missing data will be considered to have an Indeterminate response. By definition, subjects with indeterminate response will be included in the denominator for analyses in the MITT analyses set effectively counting these as unfavorable responses. A sensitivity analyses in which subjects with Indeterminate outcome in the MITT analyses set are imputed as having a favourable response will also be conducted using the same statistical methods as for the primary analysis.

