## Statistical Analysis Plan (SAP) for Protocol W-4873-301

[figure not shown]

vPrior medications that have been administered within 14 days before the date of signing the informed consent or during the Screening Phase will be recorded in the electronic Case Report Form (eCRF). All medications administered after the first dose of the study drug must be recorded in the eCRF.

wBest possible efforts should be made to conduct an in-person visit. In the event that an in-person visit is not possible due to any reason, assessment may be conducted through a telephone contact.

[figure not shown]**9. SAMPLE SIZE**

This study is designed to demonstrate non-inferiority of oral nafithromycin (800 mg once daily) compared with oral moxifloxacin (400 mg once daily).

Nafithromycin will be declared non-inferior to moxifloxacin if the lower limit of the 2-sided 95% confidence interval (CI) for the difference between treatment groups (nafithromycin minus moxifloxacin) in the proportion of subjects with a favourable clinical response at Day 4 in the MITT analyses set is greater than -0.125.

In these comparisons, the margin of 12.5% has been determined based on historic data regarding the treatment effect of antibiotics.

For the determination of the study sample size, favourable clinical response rates at Day 4, obtained from studies of subjects with CABP, of 85% to 90% are projected, with an anticipated dropout rate by Day 4 of at most 5%. However, since subjects who dropout from the study prior to Day 4 will be included in the denominator for the calculation of the proportion of subjects with favourable clinical response at Day 4, an attained favourable response rate at Day 4 of 81% to 86% is anticipated in each treatment group. Based on these attained favourable clinical response rates at Day 4, a non-inferiority margin of 12.5%, and using the Farrington-Manning sample size approach for the Miettinen and Nurminen method, it has been determined that approximately 414 adult subjects (207/arm) will need to be included in the MITT analyses set in order for the statistical test to have a-priori at least 90% power at the 1-sided 2.5% significance level when the attained favourable response rate is at least 81%. Given the number of subjects needed in the MITT (N=414) analyses set and assuming a TB rate of 15%, 488 subjects will need to be enrolled into the study.

[figure not shown]

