### Partial Date

Missing day - Impute the last day of the month unless month is same as month of first dose of study drug then impute last dose date.

Missing day and month – Impute 31st December unless year is the same as first dose date then impute last dose date.

Note: For the purpose of displaying related events, events with relationship marked as “Missing” relationship will be considered as “Treatment Related”.

In case the AE end date is missing, the AE will be kept as ‘ongoing’. The duration of AE in the listing will be displayed as >xx days. Here xx days means the total duration in days from the date when the AE started till the end of the study.

Missing times, severity and causality for AEs will be queried for a value. No imputations will be made for missing times. AEs with a missing time will be considered treatment emergent if the date is on or after the first dose of the study drug, AEs with missing severity will be considered severe and AEs with a missing relationship to the study drug will be considered related to the study drug.

- For the primary efficacy outcome at Day 4, subjects with missing data will be considered Indeterminate response. By definition, subjects with Indeterminate response will be included in the denominator for analyses in the MITT analyses set.
- Missing values for other efficacy outcomes will be handled in a similar manner as the primary efficacy outcome.
- For evaluations at the TOC Visit, subjects with Indeterminate response will be included in the denominator for analyses in the MITT analyses set and will be excluded from the CE analyses set at TOC.

[figure not shown]

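### Both missing-data rules for the Day 4 endpoint treat the arms alike, so no planned analysis lets missing outcomes be worse on nafithromycin than on moxifloxacin

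*SAP*

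**What the plan says.** Section 19.1 defines missing Day 4 data as Indeterminate and keeps those subjects in the MITT denominator. Section 23 repeats the rule: "subjects with Indeterminate response will be included in the denominator for analyses in the MITT analyses set". Section 19.2 acknowledges that this amounts to scoring them as unfavourable.

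Section 19.2 lists two sensitivity analyses for the primary outcome. Item 1 stratifies the Miettinen-Nurminen comparison by PORT class and leaves the missing-data rule alone. Item 2 is the only one that changes that rule: Indeterminate MITT subjects "are imputed as having a favourable response will also be conducted using the same statistical methods as for the primary analysis". It applies to both arms.

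The SAP has no tipping-point analysis, multiple imputation or rule that differs by arm. On the amount of missing data, section 9 plans "with an anticipated dropout rate by Day 4 of at most 5" per cent, and "an attained favourable response rate at Day 4 of 81% to 86% is anticipated in each treatment group". It states no difference in dropout between arms.

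**The concern.** A missing-data sensitivity analysis should show how far the conclusion depends on outcomes that nobody observed. For a non-inferiority claim, the assumption that threatens the conclusion is that missing subjects did worse on the test drug than on the control. The primary rule is failure in both arms and the planned check is success in both arms. Neither lets the unobserved outcomes differ between arms.

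With equal numbers missing, the same count is added to both numerators. The difference stays fixed while both rates move towards 100%, where the variance is smaller. The check is then easier to pass than the analysis it is meant to test, and agreement between the two says little about robustness. Equal missingness is also what section 9 implicitly plans for, with one dropout ceiling and one range of attained rates for both arms.

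**Working it through.** **Inputs.** Section 9 gives "a non-inferiority margin of 12.5" per cent, "at least 90% power at the 1-sided 2.5% significance level", an attained rate of at least 81%, and "approximately 414 adult subjects (207/arm) will need to be included in the MITT analyses set". Section 19.1 gives the two-sided 95% Miettinen-Nurminen interval. Dropout of 5% of 207 is 10.35, taken as 10 per arm. All response and missing counts below are illustrative assumptions, because the SAP gives only the 5% ceiling.

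**The plan's own figure.** With p = 0.81 in both arms, n = (1.960 + 1.282)² × 2 × 0.81 × 0.19 / 0.125² ≈ 207 per arm, or 414. Then 414 / 0.85 = 487.06, giving the stated 488. With the restricted-likelihood null variance the same inputs give 211 per arm, and exact Miettinen-Nurminen power at 207 is 89.8%. That is close enough to the stated 90% that the planning figures can serve as the frame here.

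**Interval.** With N = n1 + n2, the lower limit is the d below the observed difference that solves

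(p1 − p2 − d) / √{[q1(1−q1)/n1 + q2(1−q2)/n2] × N/(N−1)} = 1.96,

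where q1 and q2 are the maximum-likelihood rates constrained to q1 − q2 = d. Nafithromycin is arm 1.

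**Equal missingness: 207 per arm, 10 missing in each.** The planned check adds 10 to both numerators. The worst corner adds 10 to moxifloxacin only.

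| Observed favourable (nafithromycin vs moxifloxacin) | Primary lower limit | Planned check | Worst corner |
|---|---|---|---|
| 168 vs 168 | -7.59% | -6.79% (178 vs 178) | -12.06% (168 vs 178) |
| 166 vs 168 | -8.63% | -7.86% (176 vs 178) | -13.10%, fails (166 vs 178) |
| 159 vs 168 | -12.23% | -11.54% (169 vs 178) | -16.70%, fails (159 vs 178) |
| 158 vs 168 | -12.74%, fails | -12.06%, passes (168 vs 178) | -17.21%, fails (158 vs 178) |

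In each row the point difference is the same under the primary rule and the planned check. At 168 vs 168 the interval width falls from 15.2 to 13.6 points. In the last row the planned check passes a result that the primary fails. At 168 vs 168 the worst corner first fails with 11 missing per arm (-12.50006%).

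**Between the corners.** With 10 missing per arm, impute 5 of 10 favourable on nafithromycin and 9 of 10 on moxifloxacin. From 168 vs 168 this gives 173 vs 177 and a lower limit of -9.0%. From 166 vs 168 it gives 171 vs 177 and -10.0%. Both pass.

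**Unequal missingness.**
- More missing on moxifloxacin: nafithromycin 163 favourable and 5 missing, moxifloxacin 168 and 15. The primary gives -10.18% and passes. The planned check (168 vs 183) gives -14.27% and fails.
- More missing on nafithromycin: nafithromycin 163 favourable and 15 missing, moxifloxacin 172 and 5. The primary gives -11.97% and passes. The planned check (178 vs 177) gives -6.35% and passes. The worst corner (163 vs 177) gives -14.20% and fails.

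**Exact power at 207 per arm.** It is 89.8% under the primary rule (81% in both arms), 95.1% under the planned check (86% in both) and 52.9% under the worst-corner rule (81% vs 86%).

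**The case against.** A reader might infer that the non-inferiority claim is never stress-tested, or that the planned check almost cannot fail. The SAP does not support either reading. The primary rule already penalises nafithromycin when more nafithromycin data are missing, because those subjects count as failures. When more moxifloxacin data are missing, the planned check is the harsher of the two and can overturn a pass, as the 163 vs 168 example shows. Each rule is therefore adverse to the test drug under one direction of imbalance.

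The worst corner is also a severe yardstick. It assumes that every missing subject failed on one arm and succeeded on the other, in a double-blind trial. An equally effective drug would fail it nearly half the time (power 52.9%). At equal observed responses with 10 missing per arm it still passes, and the intermediate cases above pass too. These objections stand, and they rule out using the worst corner as a pass/fail criterion.

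Two further objections stand only in part. Section 19.1 requires Indeterminate counts by arm, so a reader could build the grid from the report, but that does not make it a prespecified analysis. The Day 4 analysis in the CE set gives an indirect look. However, that set is selected on compliance and TOC evaluability, and the analysis is not an imputation check on the MITT set.

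**Conclusion.** The point holds as a gap in the sensitivity analysis. It is not an error in the primary test, whose decision rule, type I error and power are unaffected. Both planned rules are symmetric between arms, so outcomes missing to nafithromycin's disadvantage are not examined, and under equal missingness the planned check is more lenient than the primary.

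The size depends on where the primary result falls. At about the 5% ceiling, moving from the primary rule to the worst corner costs about 4.5 points of lower limit (-7.59% to -12.06%, or -8.63% to -13.10%). A result as far inside the margin as 168 vs 168 survives even the extreme bound. One such as 166 vs 168, nearly 4 points inside the margin under the primary rule, does not. Failing at that corner would not by itself show that the result is fragile. What matters is how plausible the failing assumptions are, and the present plan gives no way to see them. The figures rest on 207 per arm and on assumed response and missing counts.

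**What to change.** In section 19.2, extend item 2 to a two-way tipping-point grid in the MITT set. One axis is the number of Indeterminate nafithromycin subjects imputed favourable (0 to all), the other the same number for moxifloxacin. Each cell gives the Miettinen-Nurminen 95% lower limit, computed as in the primary analysis. Report where -12.5% is crossed and discuss how plausible that region is, using the reasons for missingness by arm. State in advance that the worst corner is an extreme bound and not a pass/fail test. The present analysis stays as the all-favourable cell, and the primary analysis is the none-favourable cell.

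The cost is one programmed table from data already collected, with no change to the primary analysis or the sample size. The downside is that it may show a less favourable bound than the current check.

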### 19.3 Secondary Efficacy Analysis

The secondary analyses variables are listed in section 17.2. For each by-subject secondary efficacy outcome, the number and percentage of subjects with each response category (e.g., for the clinical outcome at EOT response is Cure, Failure or Indeterminate) will be summarized by treatment group.

The 2-sided 95% CI for the difference between treatment groups in the proportion of subjects with favourable response (e.g., for the clinical outcome at EOT: the difference between treatment groups in proportions of subjects with clinical cure at EOT) will be presented using the same approach as for the primary analyses. These analyses will be done for the outcomes/visits/analyses set combinations shown below (Table 2).

**Table 2. Secondary Analysis Variables by Visit and Analyses Set.**

| Analysis Variable                        | Visit       | Analyses set |       |             |
|------------------------------------------|-------------|--------------|-------|-------------|
|                                          |             | MITT         | mMITT | CE (at TOC) |
| Clinical Response                        | Day 4       | NA (primary) | X     | X           |
| Investigator-determined Clinical Outcome | EOT         | X            | X     | X           |
|                                          | TOC         | X            | X     | X           |
| Hospital re-admission Rates              | Prior to FU | X            |       |             |

Abbreviations: CE = Clinically Evaluable; MITT = Modified Intent-to-Treat; mMITT = Microbiological Modified Intent-to-Treat; TOC = Test of Cure

Similar tabulations will be done for the by-subject favourable clinical response at Day 4 and the by-subject investigator-determined clinical cure rate at TOC in subjects with bacteremia and in subjects with at least one multi-drug resistant (MDR) pathogen, defined as resistant to 2 or more antibiotics belonging to different classes (e.g., macrolides, beta-lactams, fluoroquinolones and tetracyclines) using both the US Food and Drug Administration Susceptibility Test Interpretive Criteria (FDA STIC) and the European Committee on Antimicrobial Susceptibility Testing (EUCAST) interpretive criteria and

[figure not shown]

identified from an appropriately collected respiratory specimen or blood in the mMITT analysis set, except that CIs will not be included if less than 10 subjects per treatment group are obtained.

The clinical response at day 4 as well as the investigator-determined clinical outcome at TOC will be summarized for the following subgroups in the mMITT analyses set:

- Subjects with any monomicrobial infection
- Subjects with monomicrobial infection caused by Gram-negative pathogens
- Subjects with monomicrobial infection caused by fastidious Gram-negative pathogens
- Subjects with monomicrobial infections caused by non-fastidious Gram-negative pathogens
- Subjects with monomicrobial infections caused by Gram-positive pathogens
- Subjects with monomicrobial infections caused by atypical pathogens
- Subjects with any polymicrobial infections [Note: subjects with both typical (single typical or of the same Gram type is  $> 1$ ) and atypical pathogen are included here]
- Subjects with polymicrobial infections due to Gram-positive pathogens only
- Subjects with polymicrobial infections due to Gram-negative pathogens only
- Subjects with polymicrobial infections due to atypical pathogens only
- Subjects with polymicrobial infections due to typical pathogens only of the same Gram type
- Subjects with mixed Gram-positive and Gram-negative Infections
- Subjects with mixed Gram-positive and Gram-negative Infections without atypical pathogens

The by-pathogen favourable clinical response at Day 4 and also the by-pathogen clinical cure rate at TOC will be summarized in the mMITT analyses set.

In the by-pathogen summaries, typical pathogens will be categorized as Gram-negative-fastidious, Gram-negative non-fastidious and Gram-positive.

The by-pathogen favourable clinical response at Day 4 and also the by-pathogen cure rate at TOC will also be summarized in the mMITT analyses set for:

- Subjects with monomicrobial infections due to typical pathogens
- Subjects with monomicrobial infections due to atypical pathogens
- Subjects with polymicrobial infections
  - Subjects with polymicrobial infections due to typical pathogens only
  - Subjects with polymicrobial infections due to typical and atypical

[figure not shown]

pathogens

- Subjects with polymicrobial infections due to atypical pathogens only

The incidence of superinfections and new infections will be summarized and listings by pathogen will be provided for each treatment group. In addition, subjects in the mMITT analyses set, whose baseline pathogen(s) has a decreased susceptibility (defined as a 4-fold increase in the baseline MIC) to the study treatment received in a post-baseline culture will be listed.

An assessment of hospitalisation (defined as re-admission to the hospital if previously hospitalised on or after study drug initiation [Day 1] and before FU or initial hospital admission [if not previously hospitalised] for any reason between the initiation of the study drug (Day 1) and before FU will be summarized using frequency and percentage for subjects in MITT analyses set.

Descriptive summaries of the changes from baseline/return to pre-morbid at each study visit will be generated for each individual CABP symptom: dyspnoea, cough, production of purulent sputum and pleuritic chest pain. For visits prior to the EOT visit a favourable symptom outcome will be defined as an improvement from baseline in the given symptom. For the EOT and TOC visits, Favourable symptom outcome will be defined as complete resolution or return to pre-morbid of the baseline symptom. Since not all symptoms may have been present at baseline, symptoms with No change will also be included.

## 19.4 Subgroup Analysis

Subgroup analyses for the Favourable clinical Response at Day 4 in the MITT analyses set will be presented. Subgroups are as follows:

### Demographic and Baseline Characteristics

- Age groups (Group 1: <50 years, ≥50 years, Group 2: <65 years, ≥65 years, Group 3: 65 to 75 years, Group 4: <75years, ≥75 years)
- Gender
- Race
- BMI (kg/m^2) categories (< 18.5 (underweight), 18.5 to < 25 (normal), ≥ 25 to < 30 (overweight), ≥ 30 to < 35 (obese) or ≥ 35 (morbidly obese) )

### Markers for CABP- Clinical Parameters

- PORT Risk Class (II, III/IV)
- Subjects with and without prior systemic antibiotic usage within 72 hours of randomization.
- Subjects with and without presence of SIRS (Systemic Inflammatory Response Syndrome) defined as the presence of at least 2 of: Body temperature >38°C or < 36°C, heart rate > 90 beats/min, respiratory rate > 20 breaths/min, WBC < 4,000 cells/mm^3 or > 12,000 cells/mm^3 or the presence of >10% immature neutrophils

[figure not shown]

(band forms)

- Fever (Yes and No) ( tympanic temperature  $> 38.0^{\circ}\text{C}$  [ $100.4^{\circ}\text{F}$ ] or  $< 36.0^{\circ}\text{C}$  [ $95.5^{\circ}\text{F}$ ])
- Auscultatory findings (Absent/Present)
- Presence of bacteremia at baseline (Yes and No)
- Presence of hypoxia (Yes/No) ( $\text{PaO}_2 < 60$  mmHg or  $\text{O}_2$  saturation  $< 90\%$ )
- Pleural Effusion (No, unilateral, bilateral )
- CABP involvement: Unilateral and Unilobar, Unilateral and multi-lobar, Bilateral

**Co-Morbid Conditions**

- Tuberculosis (Never, Past History, Active Tuberculosis)
- COPD (Y/N)
- Prior pneumonia (Y/N)
- History of cancer in the lungs (Never/Past History)
- Smoking History (Never, Past, Current)
- Baseline Creatinine clearance (mL/min) group ( $< 30$ ,  $\geq 30$  to  $\leq 60$ ,  $> 60$  to  $\leq 90$  or  $> 90$ ). Baseline Creatinine clearance values obtained from the central laboratory will be used. For subjects without a value obtained from the central laboratory, the baseline value from the local laboratory will be used, if available.

[figure not shown]

## **20. SAFETY ANALYSES**

Safety data will be presented based on the Safety Analyses set.

Safety will be evaluated by presenting summaries of AEs, vital signs, laboratory evaluations (hematology, chemistry panel, urine analysis) and ECG parameters.

For each safety parameter, unless otherwise stated, the last assessment made before the first administration of the study drug will be used as the baseline value.

### **20.1 Adverse Events**

A treatment-emergent adverse event (TEAE) is defined as an adverse event that occurs during or after the first administration of study drug and up through the FU visit or a pre-existing AE that worsens in severity after study drug administration.

All TEAEs will be classified by using the MedDRA (Version 25.1) System organ class (SOC) and preferred term (PT)

The number and percentage of subjects who experienced at least one TEAE will be summarized by treatment group, SOC and PT. Although a subject may have two or more TEAEs, at each level of summarization, the subject is counted only once. The same subject may contribute to two or more PTs in the same System Organ Class category.

In TEAE summaries, the primary system organ class will be presented alphabetically and the preferred terms will be sorted within primary SOC alphabetically.

The following adverse event summary tables will be produced by treatment and overall:

- Overall Summary
- TEAE by SOC and PT
- Treatment Emergent SAE by SOC and PT
- TEAE by SOC and PT summarized by Severity (for multiple occurrences of the same TEAE, the worse severity (mild, moderate or severe) will be used)
- TEAE by SOC and PT summarized by Relationship (Related, not related. For multiple occurrences of the same TEAE, the most related one will be used)

TEAEs and drug-related TEAEs will also be summarized by treatment group, SOC and PT for the subgroups defined by: PORT risk class, Gender (Male or Female), Age categories (<50 years, ≥50 years, <65 years, ≥ 65 years; 65 to 75 years; < 75 years, ≥ 75 years), BMI (kg/m^2) categories (< 18.5 (underweight), 18.5 to < 25 (normal), ≥ 25 to < 30 (overweight), ≥ 30 to < 35 (obese) or ≥ 35 (morbidly obese)), and Baseline Creatinine Clearance (mL/min) group (< 30, ≥ 30 to ≤ 60, > 60 to ≤ 90, or > 90).

All safety data, including physical examination and urinalysis results (as available), will also be provided in by-subject listings.

